#### Inclusion criteria

To be eligible to enter the study, participants must meet the following criteria:A community-dwelling older person with chronic conditions and complex care needs, defined as having multiple morbidities or a social situation that requires the attention of multiple healthcare providers or facilities,○ who is 70 years or older for non-Aboriginal and Torres Strait Islander participants, or 50 years or older for Aboriginal and Torres Strait Islander participants; or○ who is younger than the previous age criteria but has documented chronic or complex age-related conditions (previously only associated with older persons), such as early-onset dementia or arthritis, or another condition.

#### Exclusion criteria

Residents of residential aged care facility or nursing homes.Currently receiving specialist geriatrician intervention and/or care coordination, such as the Transition Care Program.

### Intervention and comparison

The OPEN ARCH intervention has two components: fast-track specialist geriatric assessment via a community-based referral to a geriatrician in local GP practices; and an enablement service offering coordination and implementation of health and social care services customised to patient need in the community. The OPEN ARCH intervention will be delivered within primary healthcare. Patients who are deemed eligible by GP screening evaluation and meet inclusion criteria will be invited to provide informed consent. 

During the first interview and assessment, the geriatrician will provide an in-depth, standardised comprehensive geriatric assessment (CGA), a multi-dimensional, interdisciplinary process used to quantify an older individual’s medical, psychosocial and functional capabilities, including diagnosis, identification of problems, goal-setting and forming an individualised comprehensive management plan for holistic treatment, rehabilitation, support and follow up [19]. Alternatively, if the participant is unable to attend the assessment at the practice, a geriatrician will offer a home visit. The type and number of referrals to primary allied healthcare professionals and community support services will be determined by individual clinical needs and delivered in the community (GP, allied health practice or community health centre) or at home. Examples of allied health services that will be offered include: occupational therapy, physiotherapy, dietetics and social work. Community social support services such as personal care assistance, meals and domestic assistance will be arranged through My Aged Care and community health providers.

Upon completion of the initial interview and assessment, the geriatrician and enablement officer will meet with GP via face-to-face case conferencing, to complete the CGA with recommendations. The following Medicare Benefits Schedule (MBS) items will be available to GPs to claim: Item Numbers 735, 739 and 743 [20].

Based on the CGA recommendations, the enablement officer will meet with participants to develop individual care plans. The enablement officer, who is an advanced health professional specialising in aged care, will further coordinate the participant’s community care by linking them with existing services. Although a registered clinician, their role is not to provide discipline specific services, but rather to draw on existing public, private and non-government allied health, nursing and social support services available in the community to facilitate care coordination goals. All participants will continue to consult with their GPs for usual medical care.

The baseline (pre-intervention or standard care) level of service provision for older patients includes referrals to the Cairns Hospital Outpatient clinic without multidisciplinary care coordination or referral to teams, such as the Aged Care Assessment Team.

### Blinding

As OPEN ARCH requires active involvement, it would not be possible to blind participants or GPs (clusters), nor enablement officers or the project manager [15]. Participants and GPs will be required to make an informed decision for consent, so they will have full disclosure available prior to the consent. Enablement officers providing clinical care will have full knowledge of the participants’ health status throughout the study period. Similarly, the project manager, who will be required to enter the data, will remain un-blinded throughout the study. However, every attempt will be made to blind outcome assessors in order to reduce information or ascertainment bias [21]. Directly asking outcome assessors which intervention they think was administered will judge the success of blinding.

### Clinical outcomes

#### Primary outcome measures

The primary outcome is service utilisation including: Emergency Department (ED) presentations, hospital admissions, in-patient bed days, allied health and support services utilisation. Hospital and ED data will be extracted from Queensland Health routinely collected computerised patient activity records. The number and type of appointments with the primary care physician and community-based allied health, nursing and social support services will be collated from medical clinic records kept by the engagement officers. A purpose-built data input form will be used to collate health and support service usage.

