### Staffing

For the purposes of this study, the following staffing will be recruited: a project manager, who will facilitate GP engagement, patient recruitment and consent, data collection, data management and reporting; a community-embedded specialist in geriatric medicine to provide comprehensive geriatric assessments and management plans at the GPs’ rooms; and two community-based care coordinators (enablement officers), who will facilitate access to healthcare services, social supports and self-management options. These positions are solely community embedded, designed to coordinate hospital-based specialist geriatric and other primary care services, such as social care services, allied health and rehabilitation services.

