#### Frequency of analyses

All data will be collected at baseline ‘0’ with retrospective collection for 3 months to time point ‘– 1’, following every 3 months of data collection, at time points ‘1’, ‘2’ and ‘3’ (see Fig. 2), except for participants’ experiences, which will be collected at the end of the study period.

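### Community service contacts are counted from records kept by officers who, on the natural reading, deliver the intervention, so this part of the primary outcome is open to differential ascertainment

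*Protocol article*

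**What the plan says.** All references are to the protocol article.

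- **Outcome.** Primary outcome measures lists "Emergency Department (ED) presentations, hospital admissions, in-patient bed days, allied health and support services utilisation".
- **Hospital source.** The same section states: "Hospital and ED data will be extracted from Queensland Health routinely collected computerised patient activity records".
- **Community source.** Primary care appointments and contacts with "community-based allied health, nursing and social support services will be collated from medical clinic records kept by the engagement officers"; a purpose-built form is used for collation.
- **Officers.** Staffing names "two community-based care coordinators (enablement officers), who will facilitate access to healthcare services, social supports and self-management options". No post called engagement officer is listed.
- **Role.** Intervention and comparison gives, as one of two components, "an enablement service offering coordination and implementation of health and social care services customised to patient need in the community". The enablement officer develops the care plan after the geriatric assessment and then links the participant to services.
- **Comparator.** Standard care includes "referrals to the Cairns Hospital Outpatient clinic without multidisciplinary care coordination".
- **Timing.** Frequency of analyses has data collected at baseline "with retrospective collection for 3 months to time point" −1, then every 3 months.
- **Second description of the source.** Economic evaluation has the project manager collate resource use from routine activity records and medical clinic records.
- **Blinding.** Enablement officers and the project manager are unblinded. An attempt will be made to blind outcome assessors.

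**The concern.** The hospital measures come from a system that records events whatever a participant's exposure. The community measures are taken from records kept by officers whose contact with the participant depends on exposure. Once a participant is under care coordination, the officer arranges allied health and support services and so knows about them. Before that, standard care has no coordinator whose work would generate the same record, and the first window is reconstructed retrospectively.

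If capture improves when a cluster crosses over, part of any apparent rise in community service use under OPEN ARCH would be better recording. This matters because two of the five listed primary measures, allied health and support services, depend on this source, and GP appointment counts are drawn from it too. More community service use is also an expected result of linking people to services, so a real increase and a recording increase point the same way and cannot be told apart afterwards.

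**Working it through.** The plan states no figure for completeness of recording, so there is nothing to reproduce. The check has three parts: whether the source depends on exposure, whether the planned analysis would remove a capture difference, and how large such a difference would need to be.

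**1. Dependence on exposure.** Primary outcome measures assigns the record to the engagement officers. Staffing lists only enablement officers, and Intervention and comparison makes them a component of the intervention that starts work after the geriatric assessment. Standard care has no care coordination. No separate source is stated for community contacts in control periods. Economic evaluation refers to medical clinic records but does not say that these differ from the officers' records.

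**2. Would the model remove it?** Statistical methods specifies a generalised linear mixed model with time and intervention status as fixed effects and clusters and clients as random effects. Write X = 1 for a cluster-period under intervention and 0 otherwise, and let s1 and s0 be the shares of true contacts captured under intervention and control. On a log scale:

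log(expected recorded count) = period effect + θX + log(s0) + X·log(s1/s0) + random effects

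The coefficient on X is therefore θ + log(s1/s0). Period effects absorb only changes common to all clusters at the same time. A change that follows each cluster's own crossover goes into the intervention coefficient. Blinded assessors do not help either, because they cannot restore contacts missing from the source record.

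**3. Size, with assumed capture shares.** Observed rate ratio = true rate ratio × s1/s0. None of the capture values below is in the document.

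| s1 | s0 | s1/s0 | True 1.00 observed as | True 0.91 observed as |
|---|---|---|---|---|
| 0.95 | 0.95 | 1.00 | 1.00 | 0.91 |
| 0.95 | 0.90 | 1.06 | 1.06 | 0.96 |
| 0.95 | 0.80 | 1.19 | 1.19 | 1.08 |
| 0.95 | 0.60 | 1.58 | 1.58 | 1.44 |

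A capture ratio of 1/0.91 = 1.10 would hide a 9% reduction completely; with s1 = 0.95 that is s0 = 0.95 × 0.91 = 0.86. The 9% is only a yardstick here, because Sample size sets it for ED and in-patient use.

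The first row shows the remedy: incomplete capture does no harm to the ratio as long as it is equally incomplete in both conditions.

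**The case against.** The strongest reply is that the document never says control-period records are absent or poorer. The phrase used is medical clinic records, and Economic evaluation has the project manager collating such records and cites objective data as a guard against recall bias. Read together, the officers may simply hold or abstract clinic records. Secondary outcomes measures has the engagement officers share data collection, and Frequency of analyses schedules collection every 3 months, so they may well see participants in control periods. That engagement officer means enablement officer is an inference. An article may also leave abstraction procedures to the full protocol.

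Much of this stands. A reader might infer that control-period records do not exist and that the comparison is therefore biased; the text supports neither. Control-period contact would narrow the gap between s1 and s0. A reader might also infer that the whole primary outcome or the whole economic evaluation is compromised. The hospital measures are independent of the officers, and the research question on hospital demand uses only those. The costs named under Economic evaluation are mainly personnel time, taken from a time log, and hospital use. If control-period community costs were understated, the error would count against OPEN ARCH.

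What does not stand is that this is only missing detail. The article makes an explicit choice of record keeper. The benign reading does not fully dispose of the point either: Ethical issues says that enablement officers' assessment, planning and progress notes are sent to the GP for upload to the patient's record, so GP records may also become fuller after crossover.

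**Conclusion.** The concern holds as a structural risk, not as a demonstrated bias. Counts of GP, allied health, nursing and support-service contacts are open to capture that changes at crossover, and the planned model would attribute such a change to the intervention. The likely direction is over-counting under OPEN ARCH relative to control periods. The size is unknown: the assumed scenarios give spurious ratios from 1.06 to 1.58, and equal capture would give none. ED presentations, admissions and bed days are unaffected.

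The conclusion rests on two assumptions: that the engagement officers are the enablement officers, which is the natural reading since no other officer post is listed, and that their knowledge of a participant's service contacts increases once coordination begins.

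**What to change.** 1. Reconcile Primary outcome measures with Economic evaluation on which records supply community contacts and who collates them, and use one term for the officers.
2. Abstract community contacts in both conditions from the same source that does not depend on exposure (GP practice or provider records), on the purpose-built form, over identical 3-month windows including the retrospective one.
3. Exclude contacts known only from officer notes, including notes uploaded to the GP record. Without this exclusion, moving to GP records would carry the same problem with it.
4. If equal capture cannot be assured, report these measures as delivery data and do not interpret them as a primary intervention effect.

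The form and access to clinic records are already planned, so the change is mainly to the abstraction instruction. It does have a cost: Trial status puts the study 6 months past baseline in November 2018, so some periods already collected would need re-abstraction. Contacts known only to the officers would go uncounted, which lowers the totals but keeps the comparison like for like. The project manager is unblinded, so a written abstraction rule applied identically in every window is needed whoever does the work.

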#### Secondary outcomes measures

Secondary outcomes will comprise: functional status as measured by the Functional Independence Measure [22] and Seniors at Risk (ISAR) screening tool [23]; quality of life (QoL) as measured by EQ-5D-5L [24] and AQOL-8D [25]; and patient experience of the OPEN ARCH intervention collected via the PSQ-18 questionnaire [26]. The secondary outcomes data collection will be shared between the project manager and engagement officers.

### Statistical methods to assess intervention effect

The primary outcome measures, including Emergency Department (ED) presentations, hospital admissions, in-patient bed days, allied health and support services utilisation, will be analysed as panels between each cross-sectional time point of the stepped wedge design, comparing primary outcomes within and between clusters. Each cross-section will include participants undertaking the intervention as well as those receiving standard care (pre-intervention component). In addition to assessing intervention effects, the stepped wedge design can also model the effects of time to determine whether the time of intervention (intervening early versus intervening late) impacts the effectiveness of the intervention. Secondary outcome measures, including functional status, ISAR and QoL measures, will be compared for the pre versus post intervention periods, for each participant, and thus the participants will act as their own control. Participants’ experience of the OPEN ARCH intervention as measured by the Likert scale responses will be analysed using descriptive statistics.

Within-cluster and between-cluster variance, treatment outcomes for intervention versus pre-intervention, across time, will be examined by applying a generalised linear mixed model (GLMM), as recommended for small cluster designed stepped wedge studies [16]. GLMM models can be adjusted for unequal numbers within clusters and cope with non-parametric data distributions. Within the GLMM, primary and secondary outcomes will be assessed against time and intervention status, represented as fixed effects, while study clusters and clients will be represented in the model as random effects [16]. Secondary outcome analyses will include *t* tests (for continuous data), chi-square tests (for proportions) and GLMMs where applicable, to control for demographic differences. All statistical tests will be two-sided and performed using a 5% significance level with no adjustment for multiplicity. Data analysis will be performed using STATA version 15 [18].

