### Randomisation of general practitioners

All recruited GPs will be randomised as ‘clusters’ at baseline using simple randomisation [17]. Such cluster randomisation allows control for the ‘between GPs variance’. A minimum of two clusters (two GPs) will be commencing the intervention at each step, as per the recommendations of Barker et al. [16], to ensure that the intervention effect estimator maintains the nominal 5% significance level and is reasonably unbiased. All clusters will ultimately receive the intervention for the same length of time.

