### Participants’ eligibility criteria

#### Sample size

Bird et al. [5] reported suitable comparative outcomes from a similar study. Following the stepped wedge study design with repeated cross-sectional samples recommendations of Barker et al. [16] and the applied parameters of Bird et al. [5], at least two clusters will be randomised at each step to ensure the nominal 5% significance level. Bird et al. [5] reached statistical significance using ANOVAs and *t* tests over three measures: ED presentations, hospital admissions and bed days. Pre verses post improvement for these three measures was 10%, 25% and 18% respectively. Following consultations with clinical and statistical experts, a conservative effect size across ED and in-patient services utilisation of 9%, a 10% intra-cluster correlation and between-cluster variations of 30% were assumed for the current study. The intervention will be staged in steps, each with at least two clusters/GPs, totalling a minimum of 10 GPs (clusters), who will each recruit 10–12 participants to the study. Allowing for 25% censoring, a sample size of 120 participants will be required, which will provide 80% power to detect a 9% difference (effect size) in service utilisation with statistical significance at the 5% level. The study design incorporates the effects of ‘time’. Sample size calculations were performed using the stepped wedge command in STATA 15 [18].

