### Economic evaluation

The economic research question is whether the OPEN ARCH intervention is cost-effective in reducing hospital utilisation and enhancing health-related quality of life when compared to the standard care. The perspective for the evaluation model will be a healthcare provider in the Australian setting [27].

Costs of the intervention will be incurred during the CGA and management. The CGA and management costs include the average time with each participant of different personnel, such as a GP, community-embedded specialist in geriatric medicine and community-based care coordinator. Costs of consecutive ED presentations, hospital admissions and hospital length of stay will be included. The cost of the pre-intervention care will include healthcare services utilisation before the initial GP consultation and CGA. Trial initiation, patient accrual and pre-screening activities as well as research and evaluation costs will be recorded and reported separately [28, 29].

Resources will be measured on a patient-specific basis obtained from the purpose-built data input form collated by the project manager from routinely collected computerised patient activity records and medical clinic records, following informed consent processes. Utilisation of objective data is known to eliminate patient recall bias and reduce the amount of missing data [30]. The cost of the time will be derived from a log of time spent on direct patient care activities. A top-down approach will be used to value resource use for capital and operating costs. Healthcare resource use data will be valued using Australian Independent Hospital Pricing Authority standard costs [31] reported in 2018 AUS$.

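### The economic evaluation ends standard care at each participant's own assessment rather than at the GP's randomised step, so hospital stays that delay the assessment are costed to standard care

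*Protocol article*

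**What the plan says.** All references are to the Protocol article.

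- **Unit and timing of randomisation** (Randomisation of general practitioners): "All recruited GPs will be randomised as ‘clusters’ at baseline using simple randomisation", and "A minimum of two clusters (two GPs) will be commencing the intervention at each step". The randomised quantity is the date on which a GP's cluster crosses over.
- **Cost boundary** (Economic evaluation): "The cost of the pre-intervention care will include healthcare services utilisation before the initial GP consultation and CGA". The same section then forms the ICER from mean cost and mean QALYs in the intervention and pre-intervention periods. ED presentations, admissions and length of stay are among the costs.
- **Where the CGA happens** (Intervention and comparison): at the GP practice, or by home visit for those unable to attend. No assessment in hospital is described.
- **Primary analysis** (Statistical methods to assess intervention effect): outcomes are analysed as panels between the time points of the stepped wedge, using a mixed model with time and intervention status as fixed effects. The section says "Each cross-section will include participants undertaking the intervention as well as those receiving standard care (pre-intervention component". It gives no date or event at which status changes.

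**The concern.** A stepped wedge is protected by randomisation only if exposure follows the allocated step. The economic evaluation uses a later date that depends on the participant's own health. Someone in hospital when the assessment is due cannot be assessed at the practice or at home, so the boundary moves to after discharge and the stay becomes a standard-care cost. Someone who dies before assessment has all costs, including any terminal stay, in the pre-intervention period. Everyone who enters the intervention period does so alive and out of hospital.

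The outcome thus helps to decide the exposure. This is immortal-time bias with reverse causation, and it always runs in favour of OPEN ARCH. At stake are the hospital-cost part of the ICER and the net monetary benefit, on which the protocol bases its cost-effectiveness conclusion.

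**Working it through.** **Plan's own figure.** The plan gives no figure for this boundary. The nearest yardstick is the planned effect in Sample size: "a conservative effect size across ED and in-patient services utilisation of 9%, a 10% intra-cluster correlation and between-cluster variations of 30% were assumed". The scale of the 9% is not stated.

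**Inputs from the protocol.** Data run from 3 months before baseline to 9 months after, in 3-month intervals. Each step has at least two GPs with 10–12 participants each, so 2 × 10 = 20 to 2 × 12 = 24 assessments, and Staffing lists one geriatrician. A lag between step and CGA is a fair inference, but its length is not given.

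**Assumed inputs (none are in the protocol).** Steps at 0, 3 and 6 months; 0.3 admissions per person-quarter; mean stay L of 5, 7 or 10 days; CGA 4–8 weeks after the step, postponed if the participant is in hospital that day or was in the previous week; no true effect.

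**Closed-form check (simple before/after split at the CGA).** Let λ be admissions per day, with stays exponential and the CGA on the first day out of hospital.

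- The chance of being in hospital on the due day is λL, and the remaining stay then averages L. So λL² extra bed days fall before the boundary.
- The intervention period starts with everyone out of hospital, so it falls short of the steady-state total by the same λL².
- Ignoring the small change in period length, the bed-day rate ratio is [λL − λL²/T_int] ÷ [λL + λL²/T_pre] = (1 − L/T_int) ÷ (1 + L/T_pre). The admission rate cancels.
- With 91-day quarters, a mean step of 91 days and a mean lag of 42 days: T_pre = 91 + 91 + 42 = 224 days, and T_int = 4 × 91 − 224 = 140 days.

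| Mean stay | Calculation | Ratio |
|---|---|---|
| 5 days | 0.964 ÷ 1.022 | 0.94 |
| 7 days | 0.950 ÷ 1.031 | 0.92 |
| 10 days | 0.929 ÷ 1.045 | 0.89 |

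**Simulation under no effect, same assumptions.** This adds postponement in the week after discharge.

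| How time is classified | Bed-day ratio |
|---|---|
| Randomised step | about 1.0 |
| Day of own CGA, simple before/after | about 0.88–0.93 |
| Day of own CGA, stratified by quarter | 0.79–0.90 |
| Whole 3-month panels by CGA date | 0.91–1.01 |

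As reductions: 1 − 0.93 = 7% to 1 − 0.88 = 12% for the simple split, and 1 − 0.90 = 10% to 1 − 0.79 = 21% when stratified. Adding 8% annual mortality with a terminal stay gave 0.77–0.87 by CGA date and 0.95–1.03 by step (stratified).

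**Wider assumptions.** A separate simulation used five steps, 1–4 bed days per 91 days, assessment 0–84 days after the step and rebooking after 0–28 days. Stratified by period and split on the assessment day, the ratio was about 0.91–0.95 (5-day stays), 0.87–0.89 (10-day) and 0.76–0.81 (20-day). By step it was 0.97–1.04. With whole panels it was 0.76–1.02, depending on panel convention and scheduling.

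**Which figure applies.** The ICER is built from mean costs in two periods, so the simple split is closer to what is described. The percentages refer to bed days. Total cost also includes ED presentations and the cost of OPEN ARCH itself, so its proportional change will differ.

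**The case against.** A reader might infer that the primary analysis also sets status by each participant's assessment, so that ED presentations, admissions and bed days all favour OPEN ARCH under the null. The protocol does not support that.

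- The sentence on cross-sections describes any stepped wedge: at a given time some clusters have crossed over and others have not. The text on randomisation and the panel analysis both point to the GP's step.
- How the status term is coded is detail commonly left to an analysis plan that is not shown.
- Even if status followed the CGA, whole 3-month panels give little or no bias in bed days under the main assumptions. The wider panel range above includes long stays and other scheduling, and it also includes no bias.
- For admissions, a day-level split gave ratios of 0.97–0.995, which is close to null. ED presentations were not simulated.

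All of this stands, and it confines the finding to the cost comparison.

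Two further replies carry less weight. The lag and any postponement are inferred, the assessment is described as fast-track, and home visits are offered. That affects the size, but a home visit does not reach an inpatient. The economic section also plans sensitivity analysis on the choice of comparator. It does not say that this covers the date separating the two periods, and a sensitivity analysis would not repair a base case that departs from the randomised contrast.

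**Conclusion.** The point holds for the economic evaluation. Its stated boundary conflicts with the randomised crossover, and the resulting error favours OPEN ARCH. Under the assumed rates, stays and scheduling, the spurious reduction in bed days is roughly 7–12% for a simple before/after split and 10–21% when stratified by quarter, against about nil by step. That is of the same order as the planned 9% effect. Longer stays enlarge it and shorter stays shrink it. The direction follows from the protocol's text together with a delay caused by hospital stay or death; the size rests wholly on the assumptions.

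No bias in the primary ED, admission or bed-day results is shown. The protocol leaves the status term undated there, which is a reason to align it with the step and not evidence of an error.

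**What to change.** In Economic evaluation, separate intervention from pre-intervention costs and QALYs at the GP's randomised step date for every enrolled participant, whether or when the CGA takes place. This includes those who die, are in hospital or enter residential care before assessment. Carry the same split into the ICER. In Statistical methods to assess intervention effect, state the same step-based definition of intervention status, so that the clinical and cost analyses use one exposure. Keep the split at the actual CGA date as a labelled sensitivity analysis.

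The cost is a change of wording. The step dates belong to the allocation, and no care or data collection changes. The one drawback is that the weeks between step and CGA count as intervention and slightly dilute a true effect. That is the usual price of analysing by allocation, and it does not manufacture a benefit.
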